### Sample size

Variability was estimated from the feasibility study.
^24^ Estimates of the standard deviation (SD) for systolic BP change from baseline at 4-weeks, 3 and 6-months were 12.5, 10.8 and 14.4 mmHg respectively. With a minimal clinical important difference 5 mmHg and SD of 14.4, we require 352 participants to complete this study to attain 90% power with a 5% significance level. Assuming 35% attrition we aim to randomise 542 participants, 271 in each group. The sample size confidence interval has been calculated using Pass11 software (PASS 11. NCSS, LLC. Kaysville, Utah, USA.
www.ncss.com).

For qualitative data samples, we will conduct up to four online focus groups of 6–8 participants each from the intervention group plus up to 15 interviews with stakeholders – it is expected that this sample will achieve data saturation whereby no new qualitative data codes/elements are identified when approaching the full sample.
^25^

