•sending out automated blood pressure devices for participant screening and beyond;•sending out of study documents if requested or required for accessibility reasons;•sending of a GP letter to participant’s GP practice to inform them of study participation and what this involves;•setting up access to participant portal online with digital resources including instructional videos;•mobile and email reminders of study assessments and training if assigned to IE group.

**
*Screening*
**

After successfully completing pre-screening and upon receipt of their home blood pressure monitor, they will be instructed via email to measure their blood pressure for 3 days consecutively at home, taking 3 measurements in the morning and evening according to European Hypertension Society and NICE guidelines.
^1^
^,^
^26^ Measurements will be conducted using the home BP device (Kinetik Wellbeing WBP1 model number TMB-1775-A and model TMB-2287-K for those requiring an extra-large cuff
) provided by the study which will be mailed to the participant along with an instruction sheet and participant diary. Participants are instructed to continue normal activities during the screening period. Participants are made aware in the PIS and again prior to entering their screening data that a final decision about their eligibility to participate in the study after collection of:
•past medical history (in relation to eligibility criteria)•current medication•3 days of home blood pressure measurements•confirmation of ability to do IE

The calculation of blood pressure for entry into the study is conducted using the 2nd and 3rd reading on the 3 consecutive days morning and evening (total of 12 readings used to calculate the average home blood pressure). The average of all readings for home blood pressure is conducted to ensure we aren’t including people with either overtreated hypertension, white coat hypertension or people mis-diagnosed as hypertensive. Eligibility is then assessed against the full criteria. Those who screen fail will be sent an email thanking them for their contribution to the study and provided with website links for maintaining a healthy blood pressure and lifestyle (the same standard care advice provided to all participants in the study). Those who pass screening then proceed to randomisation and enrolment in the study as below.

**
*Randomisation*
**

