### Participant on study timeline and assessments

This section describes the assessments and visits conducted with participants once they are randomised.
Table 1 overleaf summarises the schedule of assessments at each time point and
Figure 2 provides a flow chart of participant flow through the study. There are no prohibited interventions during the trial. Participants’ (control and intervention) GP’s or other relevant healthcare organisation (e.g. hospital) will continue to be responsible for normal care provision with respect to hypertension and other medical conditions through and post study participation. A letter will be sent to the participant’s GP to inform them of participation in the study and what that involves. Participants will be able to request a copy of this. Participants will be advised to seek advice and care from their GP throughout the study should their condition change. Participants will be asked not to alter medication unless absolutely necessary and after consultation with their GP. Participants with BP > 180/120 will be advised to seek urgent medical review, GPs will be advised to follow NICE guidelines in relation to urgent specialist referral.

**Table 1. T1:** Participant schedule of assessments.

Assessment	Pre- screening	Screening	Baseline Day 1 (start date of IE training)	Follow up 1 Day 30 (+/− 3 days)	Follow up 2 Month 3 (+/− 7 days)	Follow up 3 Month 6 (+/− 7 days)	Follow up 4 ^ 1 ^ Month 12 (+/− 7 days)
Pre-screening form	X						
Collection of unidentified demographic data	X						
Consent		X					
Home BP readings		X ^ 2 ^	X ^ 3 ^	X	X	X	X
Confirmed IE ability		X					
Randomisation			X				
Standard Care lifestyle advice			X				
Self-prescribing of IE ^ 4 ^			X				
Outside range RPE data ^ 5 ^				X			
Diet questionnaire			X		X	X	X
Concomitant medication			X	X	X	X	X
Exercise questionnaire			X		X	X	X
Quality of life questionnaire			X		X	X	
IE experience questionnaire				X			
Health resource use questionnaire					X	X	
Invitation to take part in study focus group				X			

1 – first n=50 invited and accepting to continue follow up until Month 12 2 - recorded between Day -7 and Day 0 3 - if Screening BP measures ≥28 days prior to baseline 4 - IE group only 5 – collected from the first n=50 participants only for fidelity assessment

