[i] 1 – first n = 50 invited and accepting to continue follow up until Month 12 2 - recorded between Day −7 and Day 0 3 - if Screening BP measures ≥28 days prior to baseline 4 - IE group only 5 – collected from the first n = 50 participants only for fidelity assessment.

**
*Baseline assessment*
**

Once the participant has been randomised, they will receive an email providing details of how to set up their log in details and enter the study website portal where they will have access to standard care lifestyle advice resources and IE exercise training videos for those in the intervention group. Participants will be instructed to start their standard care advice and IE training if assigned, at a time when they have at least 60 minutes to run through the information and are requested to complete the initial standard care advice and IE training induction within 14 days of completing the baseline questionnaire and/or no more than 28 days after they finished their 3 days of home BP readings. If not completed within this time, one final reminder will be sent before they are withdrawn from the study. If a randomised participant does not complete their standard care advice and IE training within 14 days, they will be able to start this for up to 3 months after consenting to take part, however after 14 days they will be asked to confirm that their eligibility has not changed.

**
*Follow up assessments – Week 4, Month 3, Month 6 and Month 12*
**

All participants will be followed up at week 4 (Day 30 +/−3), at months 3 and 6 (+/− 7 days). Follow up at month 12 will be conducted for a sub-group of the first n = 50 intervention group participants to evaluate longer term BP changes. This longer term, 12-month follow up is restricted to 50 participants due to the funding envelope and duration of 30 months which allows the research to explore longer term outcomes within limited time and funding whilst maintaining value for money. An invitation will be sent to the participants up to 2 weeks before finishing their 6 months of IE, to invite them to continue to 12 months and the reasons why. Invitations will be sent until there is an uptake of 50 for the subgroup.

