Participants will receive electronic reminders (email, text or WhatsApp message depending on participant preference) ahead of each follow up time point to prompt data collection. They will receive further reminders on the day of assessment and then daily during the submission window (refer to above) to submit their information through the online questionnaire. Intervention arm participants will receive reminders of exercise sessions as per their preferences set during baseline data collection. Weekly motivational messages will also be sent to control participants for the first 6 weeks of the study. This will aid adherence to the study and IE training and reminders will include a link to input their data each time or at regular weekly intervals. At each follow up, participants will record their home blood pressure, heart rate readings and in their participant diary and submit these via an online questionnaire using a link emailed or texted to participants. Alternative methods for data recording will be made available to participants where requested, for accessibility (telephone call, on paper etc.) and supported by local teams or the study team centrally.

The protocol requires three consecutive measurements (separated by two minutes) always using the same arm (use arm with high reading if >15 mmHg difference when first checked), to be taken in the morning and afternoon for three days at each timepoint. Home blood pressure monitoring will follow NICE and ESH/ESC guidelines
^1^
^,^
^26^ using a British and Irish Hypertension Society approved blood pressure monitor. Participants will be asked to keep their chosen times of blood pressure measurements and ingestion of medication consistent throughout the study. Adverse events, checking of medication, adapted version of UK EPIC NORFOLK Food Frequency Questionnaire,
^34^ General Practice Physical Activity Questionnaire,
^35^ EuroQOL quality of life 5D-5L questionnaire,
^36^ study-specific IE intervention experience questionnaire (intervention group only at week 4) and health economics data (questionnaire adapted for the study from
^37^) will also be collected according to the schedule of assessments (

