The primary outcome, change from baseline in systolic BP at 3-months, will be analysed using analysis of covariance, with a fixed treatment effect allowing adjustments for baseline values, sex, age, and hypertension medication status. The primary analysis will be conducted using an intention to treat approach with a two-sided 5% significance level. Secondary analysis will examine treatment effects under different scenarios for compliance with allocation/treatment, using per protocol approaches. Prior to analysis distributional assumptions will be assessed, and the data may be transformed or alternative nonparametric approaches used where there is evidence of non-normality. Data from the IE experience questionnaires will be analysed using descriptive statistics, as will secondary process outcomes such as recruitment and adherence rates, attrition and completeness of the data.

We will undertake an interim analysis of the first 50 participants’ fourth bout RPE scores and the extent to which these are in range of the target zone to check intervention fidelity to determine the extent to which the intervention is being delivered as intended. Data collected for this purpose involves confirmation from participants on whether they altered their wall squat height and whether their RPE was outside of range.

To avoid loss of efficiency, missing outcome values (both primary systolic blood pressure and secondary diastolic blood pressure) will be imputed using multiple imputation, if the proportion of missing data is greater than 5% and less than 40%.
^41^ Where there are less than 5% missing data, the proportion of missing data is considered negligible and missing observations will be excluded. Multiple imputation methods perform less well when the amount of missing data is substantial, if more than 40% of the primary outcome data are missing in the primary analysis the assumptions are less plausible. The interpretative limitations of the trial data will be discussed in the results section, where this is the case.

An imputation model containing all potential prognostic baseline covariates, the primary outcome variable at 4 weeks follow-up, and the secondary outcome variable diastolic blood pressure at 4 weeks follow-up will be used.
^42^ The number of imputations will be dependent on the amount of missing data, as a minimum the number of imputations will be derived to ensure at least 96% statistical efficiency (RE) according to the formula below, where

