We will conduct a cost consequence analysis and present evidence on a range of costs and outcomes associated with the intervention. We will present the number and percentage of participants with missing values for each cost element and each outcome measure. Data from the QOL and economic questionnaires will be transferred to STATA 18 and analysed using descriptive statistics. We will estimate the mean and 95% confidence intervals for each type of cost (intervention, NHS primary care, NHS secondary care), and the difference between intervention and control group. We will calculate the mean QOL and 95% confidence intervals for both groups both unadjusted and after adjusting for baseline utilities and we will estimate the difference between the two groups. We will also estimate the QALYs for each group at 3-months and 6-months.

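### In this open-label trial the baseline questionnaires, and apparently any repeat baseline BP, come after randomisation; they should be completed before the allocation is revealed

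*Protocol article*

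**What the plan says.** All references are to the protocol article.

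- **Order.** Under Participant enrolment (Screening), those who pass screening go on to randomisation. The section Participant on study timeline and assessments then begins: "This section describes the assessments and visits conducted with participants once they are randomised". Its Baseline assessment paragraph opens: "Once the participant has been randomised, they will receive an email providing details". Table 1 puts randomisation, the diet, exercise and quality-of-life questionnaires and the conditional repeat BP in a single Day 1 column.
- **Blinding.** The Randomisation text says participants know their group. The Study Intervention text opens the arm's resources only once baseline data are in.
- **BP baseline.** Screening BP is the average of 12 home readings taken before randomisation. Table 1 allows a second baseline BP under footnote 3: "3 - if Screening BP measures ≥28 days prior to baseline". Footnote 2 places the screening readings between Day -7 and Day 0. The Baseline assessment text sets a 28-day limit after the readings but also lets people start up to 3 months after consent.
- **Reading times.** Screening asks for "taking 3 measurements in the morning and evening". The follow-up text asks for readings "to be taken in the morning and afternoon for three days at each timepoint", and also asks participants to keep their measurement times constant.
- **Use in analysis.** The primary ANCOVA analyses change in systolic BP and adjusts for baseline. The health economic analysis reports quality of life unadjusted and "after adjusting for baseline utilities". Lifestyle change is a secondary outcome.

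**The concern.** A baseline value protects a comparison because allocation cannot have influenced it. Once participants know their arm, a self-completed questionnaire or a self-read BP can drift differently in the two groups: through expectation, disappointment at being a control, or preparing for the exercise. Subtracting such a value, or adjusting for it, carries the drift into the treatment effect with its sign reversed. Randomisation does not remove it, and a larger sample does not reduce it.

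At stake are the quality-of-life and lifestyle comparisons for all participants, and the primary systolic BP comparison for those whose BP is re-measured. The two footnotes and the two descriptions of reading times add doubt about which BP value is the baseline and how it was taken.

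**Working it through.** **1. Does baseline follow allocation?**

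| Item | Position relative to randomisation | Basis |
|---|---|---|
| Screening home BP (12-reading average) | Before | Stated in Screening |
| Sex, age group, medication status | Before | Stratification factors |
| Diet, exercise, EQ-5D | After, on the natural reading | Section opening, Baseline assessment text, Table 1 column |
| Repeat home BP | Apparently after | Same Table 1 column; the text gives no explicit order |

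One further detail points the same way. Exercise reminders for the intervention arm follow preferences set while baseline data are collected. If only that arm is asked, the form itself discloses the arm; the article does not say who is asked.

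**2. Who is exposed?** For questionnaires, everyone. For systolic BP, only those with a repeat reading. The article does not say how many that will be, nor that the repeat replaces the screening average.

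**3. The plan's own figure.** Inputs: difference 5 mmHg, SD 14.4, "to attain 90% power with a 5% significance level"; the analysis uses an "intention to treat approach with a two-sided 5% significance level".

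- Normal approximation: 2 × (1.960 + 1.282)² × 14.4² / 5² = 174.3, so 175 per arm.
- Two-sample t-test: 175.3, so 176 per arm and 352 completers, as stated.
- 352 / 0.65 = 541.5, so 542 randomised, as stated.

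The sample size is reproduced and does not depend on this point.

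**4. Possible bias in the primary analysis if the repeat reading is the baseline.** Let *f* be the share re-measured after allocation, *d* the between-arm shift in those readings caused by knowing the arm, and *b* the slope of follow-up on baseline BP. The mean baseline then differs between arms by *f·d*. A plain change score is biased by *f·d*, and the ANCOVA by *b·f·d*.

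None of the three is in the documents, so all are assumed. For the slope, a true between-person SD of 9 and a reading-error SD of 6 would give 81/117 = 0.69; a range of 0.5 to 0.7 is used.

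| *f* | *d* (mmHg) | Change score | ANCOVA, *b* = 0.5 | ANCOVA, *b* = 0.7 |
|---|---|---|---|---|
| 5% | 1 | 0.05 | 0.025 | 0.035 |
| 10% | 2 | 0.20 | 0.10 | 0.14 |
| 20% | 3 | 0.60 | 0.30 | 0.42 |
| 30% | 3 | 0.90 | 0.45 | 0.63 |

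The ANCOVA range is about 0.03 to 0.6 mmHg, or 0.5% to 13% of 5 mmHg. For comparison, the unadjusted standard error at 176 per arm is 14.4 × √(2/176) = 1.54 mmHg, or 1.15 with the 3-month SD of 10.8. If a 0.6 mmHg bias ran against the intervention, power at SD 14.4 would fall from 0.90 to 0.82. If it ran the other way, the benefit would be overstated by the same amount.

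**5. Questionnaires.** Here *f* = 1, so a shift *d* enters a change score in full and an adjusted comparison as *b·d*. The documents give no SD for these measures, so no size is offered.

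**6. Footnotes.** Readings taken between Day -7 and Day 0 are at most 8 days old on Day 1, so the 28-day condition cannot arise for anyone who keeps to footnote 2. It arises only when that window is missed, which the 3-month allowance makes possible.

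**7. Reading times.** If evening and afternoon readings differ by *k* mmHg on average, the change score moves by the same amount in both arms, and *k* cancels in the between-arm difference. It does not cancel in the 12-month change, measured only in the exercise arm, or in the proportion at target compared with baseline.

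**The case against.** The strongest reply is that the primary baseline is sound by default. The 12-reading screening average precedes randomisation, the repeat is a contingency, and participants are asked to start within 28 days of their readings. Nothing suggests that a large share will be re-measured. This stands: a reader might infer that the whole primary baseline is post-randomisation, and the documents do not support that.

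Second, the order is not explicit everywhere. Table 1 also lists pre-randomisation steps although its section is described as post-randomisation, and no sentence places the repeat BP after allocation. This stands in part: the order is inferred for the repeat BP, but well supported for the questionnaires.

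Third, resources open only after baseline data collection. That limits exercise before baseline, but it does not conceal the arm.

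Fourth, the remaining ANCOVA covariates are stratification factors, and quality of life is also reported unadjusted. Both are correct. The first means that the exposure does not extend to the whole covariate set. The second does not protect a change from an exposed baseline.

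Fifth, afternoon and evening may be loose wording for one schedule, since both passages cite the same guidance and participants are told to keep their times constant. That is plausible. A reader might infer that the mismatch biases the primary result, but a difference common to both arms largely cancels there.

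Last, a reader might call footnotes 2 and 3 mutually impossible. They can be read as a planned window and a fallback, so they need reconciling and no more.

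The choice of baseline value may also be settled in the separate Data Analysis Plan, which was not available. The ordering and the two wording conflicts are stated in the article itself.

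**Conclusion.** The point holds in limited form. The baseline questionnaires are, on the natural reading, completed by participants who can know their arm, so the quality-of-life and lifestyle baselines are exposed for everyone. The primary systolic BP baseline is exposed only for late starters with a repeat reading, and only if that reading is used as baseline. On assumed values the primary bias is about 0.03 to 0.6 mmHg against 5 mmHg, direction unknown. This is modest and smaller than the sampling error, but it is systematic and avoidable. It does not undermine the primary analysis or the sample size. The footnotes and reading times are matters of wording to reconcile. The case for acting is that the remedy is cheap, not that the expected bias is large.

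**What to change.** 1. In REDCap, require the diet, exercise and EQ-5D baseline forms, and any repeat home BP needed before allocation, to be complete before randomisation is unlocked, or at least before the allocation is shown. State this order in the Baseline assessment text and in Table 1.
2. Define baseline systolic and diastolic BP for everyone as the last home average before randomisation. A BP repeated after allocation can be kept and reported, but should not replace it.
3. Reconcile footnote 2 with footnote 3 and with the 28-day and 3-month allowances in the Baseline assessment text.
4. Reconcile the two descriptions of daily reading times so that one measurement schedule applies at screening, any repeat and every follow-up.

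The cost is re-ordered forms, a few sentences of protocol text and slightly more drop-out before randomisation, which does not bias the comparison. For late starters the pre-randomisation average will be older and may predict the outcome a little less well; that costs some precision, not validity. No change in sample size is needed.

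### Withdrawing randomised participants who do not start in time contradicts the next sentence of the protocol and the intention-to-treat primary analysis

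*Protocol article*

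**What the plan says.** The rule is in the protocol article under Participant on study timeline and assessments, Baseline assessment. That text starts after allocation: "Once the participant has been randomised, they will receive an email providing details". Participants are to complete the standard care advice, and the isometric exercise (IE) induction if allocated to it, "within 14 days of completing the baseline questionnaire and/or no more than 28 days after they finished their 3 days of home BP readings". Then: "If not completed within this time, one final reminder will be sent before they are withdrawn from the study".

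The next sentence concerns randomised participants who have not completed this within 14 days. It says "they will be able to start this for up to 3 months after consenting to take part", and adds "however after 14 days they will be asked to confirm that their eligibility has not changed".

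The follow-up paragraph of the same section says that everyone is followed at week 4, month 3 and month 6. It does not mention people withdrawn for not starting. Participant withdrawal, under Study governance, keeps data gathered before a withdrawal unless the participant objects.

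Table 1 heads one column "Baseline Day 1 (start date of IE training" and places randomisation and the standard care advice in that same column.

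Statistical methods states: "The primary analysis will be conducted using an intention to treat approach". Missing BP outcomes are excluded if under 5% are missing and multiply imputed between 5% and 40%. Above 40%, only a discussion of limitations is promised. A pattern-mixture sensitivity analysis follows if data are suspected to be missing not at random or if missingness is linked to allocation.

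**The concern.** There are three problems, and they compound one another.

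1. **Contradiction.** One sentence removes a person who misses the limit, and the next lets that person start later. Staff could apply either, and the choice decides who contributes a month 3 outcome.
2. **Conflict with intention to treat.** The text withdraws people from the study, not only from the intervention. Not starting is something that happens after randomisation and can depend on the arm. An intention-to-treat comparison needs those people's outcomes, and nothing in the article keeps them in BP follow-up.
3. **Unclear clock.** Table 1 treats randomisation and the start of training as the same day, although the late-start sentence lets them differ. If follow-up runs from the start of training, a non-starter never reaches month 3, and a late starter reaches it later after randomisation than someone who started at once.

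The trial presents itself as a test of effectiveness in real-world use, so failure to take up the exercise is part of the effect it sets out to measure. Outcomes that were never collected cannot be recovered at the analysis stage.

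**Working it through.** **The plan's own figure.** Sample size gives a 5 mmHg difference, SD 14.4, 90% power and a 5% level. The two-sample t calculation gives 176 per arm (power 0.901), hence 352 completers. Then 352 / 0.65 = 541.5, rounded up to 542, or 271 per arm. This reproduces the plan and is not in dispute.

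**Can the missing-data plan recover the effect?** For people withdrawn at this stage:
- The imputation model uses baseline covariates and week 4 BP. They would have been withdrawn before week 4, so only baseline informs their imputed value.
- The imputation carries over the primary model, which includes the treatment effect. An IE non-starter is therefore imputed like an IE starter with the same baseline.
- Below 5% missing, they are excluded.
- The pattern-mixture analysis is conditional and is a sensitivity analysis. Its data up to dropout are, for these people, baseline only.

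**Size (illustration).** Let w be the share of the IE arm that does not start; the documents give no value. Assume an effect of 5 mmHg in starters and 0 in IE non-starters, and no prognostic difference between them.
- True intention-to-treat effect = 5 × (1 − w).
- Estimate when non-starters are imputed like starters = 5 × (1 − w) + 5 × w = 5. Exclusion also gives 5.
- Relative overstatement = 1 / (1 − w) − 1.
- Power for the true effect uses 176 per arm, with SE = 14.4 × √(2/176) = 1.535.

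| w | Number of 271 | True effect (mmHg) | Estimate (mmHg) | Overstated by | Power for true effect |
|---|---|---|---|---|---|
| 5% | 14 | 4.75 | about 5.0 | 0.25 (5%) | 87% |
| 10% | 27 | 4.50 | about 5.0 | 0.50 (11%) | 83% |
| 20% | 54 | 4.00 | about 5.0 | 1.00 (25%) | 74% |

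Under these assumptions the gap depends only on w in the IE arm. Control non-starters with the same prognosis as other controls leave both the estimate and the true effect unchanged.

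**If there is no effect.** Suppose instead that IE does nothing, that only the IE arm loses people, and that those lost would have done g mmHg worse. The bias is w × g. With g = 5 it is 0.25, 0.5 or 1.0 mmHg, and the two-sided type I error is about 5.3%, 6.2% or 10%. With g = 2 the bias is 0.1, 0.2 or 0.4 mmHg and the error about 5.0%, 5.2% or 5.8%.

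**Clock.** The late-start limit runs from consent, which comes before delivery of the monitor, screening and randomisation. The possible delay after randomisation is therefore shorter than 3 months. It can still exceed 14 days, whereas the month 3 window is ±7 days.

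**The case against.** The strongest reply is that the plan does not simply drop these people. With 35% attrition assumed, multiple imputation is the expected route. Baseline data are retained, and a pattern-mixture analysis is planned for missingness linked to allocation. This stands as a correction to any claim that non-starters vanish from the analysis. It does not remove the bias, because the imputation has no information that they did not exercise.

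Some stronger readings are tempting, but the documents do not support them:
- *The loss falls mainly on the exercise arm.* The deadline covers both arms, since controls must complete the standard care advice. Greater loss in the IE arm is plausible because of the extra wall-squat induction, but no start rate is given for either arm.
- *Controls have no Day 1.* Table 1 gives them one. Only the bracketed label is specific to exercise, and no text says that the clock runs from training rather than from randomisation. The fault is ambiguity.
- *The per-protocol analyses repeat the selection.* The article mentions secondary analyses "under different scenarios for compliance with allocation/treatment, using per protocol approaches" but does not define the comparison. That detail may be in the separate data analysis plan, so no finding is made.

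A Table 1 footnote also repeats home BP when the screening readings are 28 or more days old. That partly deals with an ageing baseline after a late start, but not with the follow-up clock.

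**Conclusion.** The point holds and needs correcting before outcomes are lost. Two things are certain from the text: the withdrawal and late-start sentences contradict each other, and withdrawal from the study for not starting is incompatible with the stated intention-to-treat analysis. It is also clear that the planned imputation would not restore what is missing.

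The size is not known. Under the stated assumptions, 5% to 20% non-starters in the IE arm would overstate the intention-to-treat effect by about 0.25 to 1.0 mmHg on a 5 mmHg target. The non-starter rates and the zero effect in non-starters are assumptions. Any further bias from a prognostic difference depends on differential loss that the documents do not quantify. The time origin is ambiguous rather than demonstrably wrong.

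**What to change.** - Delete withdrawal from the study as a consequence of not starting. State that all randomised participants stay in BP follow-up and in the intention-to-treat analysis unless they withdraw consent.
- Reconcile the 14-day, 28-day and 3-month start windows. Which of them stands is for the sponsor to decide, but missing it must not end outcome collection.
- State one time origin for the week 4, month 3 and month 6 assessments. It must apply equally to both arms and exist for people who never start. The randomisation date is the natural choice.

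The cost is protocol wording and scheduling in the data capture system. The intention-to-treat effect will be somewhat smaller, and late starters will have trained for less time by month 3. If non-starting is common, power for that effect falls below the planned 90%, as the table shows.
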